**Table 6-8 Dose Modifications for Non-hematologic Toxicity**

| Recommended Action                                                                                                                                                                                                                                                                     |                                                                                                                                                                                                       |                                                                                                                                                                                   |
|-----------------------------------------------------------------------------------------------------------------------------------------------------------------------------------------------------------------------------------------------------------------------------------------------|-------------------------------------------------------------------------------------------------------------------------------------------------------------------------------------------------------|-----------------------------------------------------------------------------------------------------------------------------------------------------------------------------------|
|                                                                                                                                                                                                                                                                                               | Lenalidomide                                                                                                                                                                                   | Carfilzomib                                                                                                                                                                |
| Grade 2 – 3                                                                                                                                                                                                                                                                                   | 
Hold lenalidomide dose. Follow at least weekly.
 
If the toxicity resolves to <math>\leq</math> Grade 1 prior to Day 21, restart at 1 dose decrement and continue the cycle until Day 21.
 | Hold until $\leq$ Grade 1, reinstitute at current dose.                                                                                                                           |
| Grade 4                                                                                                                                                                                                                                                                                       | Discontinue                                                                                                                                                                                           | Discontinue                                                                                                                                                                       |
| 
Tumor lysis syndrome
 
<math>\geq 3</math> of the following: <math>\geq 50\%</math> increase in creatinine, uric acid, or phosphate; <math>\geq 30\%</math> increase in potassium; <math>\geq 20\%</math> decrease in calcium; or <math>\geq 2</math>-fold increase in LDH
 | 
Hold lenalidomide until all abnormalities in serum chemistries have resolved.
 
Reinstitute at full doses.
                                                                                | 
Hold carfilzomib until all abnormalities in serum chemistries have resolved.
 
Reinstitute at full doses.
                                                             |
| Infection Grade 3 or 4                                                                                                                                                                                                                                                                 | 
Hold lenalidomide until systemic treatment for infection is completed. If no neutropenia, restart both drugs at full dose. If neutropenic, follow neutropenic instructions.
                    | 
Hold carfilzomib until systemic treatment for infection is completed. If no neutropenia, restart both drugs at full dose. If neutropenic, follow neutropenic instructions.
 |
| Herpes zoster or simplex of any grade                                                                                                                                                                                                                                                  | 
Hold lenalidomide until lesions are dry.
 
Reinstitute at full doses.
                                                                                                                     | 
Hold carfilzomib until lesions are dry.
 
Reinstitute at full doses.
                                                                                                  |
| Grade 2 neuropathy with pain or any Grade 3 neuropathy                                                                                                                                                                                                                                 | 
Hold until <math>\leq</math> Grade 2.
 
Then restart lenalidomide at 1 dose decrement
                                                                                                     | 
Hold until resolved to <math>\leq</math> Grade 2.
 
Then restart carfilzomib at 1 dose decrement
                                                                      |

**Table 6-8 Dose Modifications for Non-hematologic Toxicity**

| Recommended Action              |                                                                                                       |                                                                                |
|----------------------------------------|-------------------------------------------------------------------------------------------------------|--------------------------------------------------------------------------------|
|                                        | Lenalidomide                                                                                   | Carfilzomib                                                             |
| Grade 4 neuropathy              | Discontinue                                                                                           | Discontinue                                                                    |
| Renal dysfunction               |                                                                                                       |                                                                                |
| Serum creatinine > 2 mg/dL             | Base dose reduction on calculated GFR (below)                                                         | Base dose reduction on calculated GFR (below)                                  |
| CrCl > 50 mL/min                       | Full dose                                                                                             | Full dose                                                                      |
| CrCl < 50 mL/min
> 30 mL/min        | Reduce lenalidomide to 10 mg every 24 h; may reinstate prior dose if, after 2 cycles, CrCl normalizes | Full dose                                                                      |
| CrCl < 30 mL/min                       | Reduce lenalidomide to 15 mg every 48 h                                                               | Hold carfilzomib until CrCl > 30 mL/min; restart at 1 dose decrement           |
| CrCl < 30 mL/min
requiring dialysis | 5 mg. Once daily. On dialysis days the dose should be administered following dialysis.                | Hold until resolved to ≤ Grade 2. Then restart carfilzomib at 1 dose decrement |

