In addition to the above observations, a phase I study of carfilzomib in patients with relapsed and refractory multiple myeloma was reported in abstract form at the 2009 American Society of Hematology meeting which demonstrated that carfilzomib can be safely administered to patients with substantial renal impairment ( $\text{CrCl} < 30$ , including patients on dialysis) without dose adjustment. These data indicate that carfilzomib does not exacerbate underlying renal dysfunction, and confirm the “pre-renal” etiology of the BUN/creatinine elevations observed with IV bolus carfilzomib.

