**Table 6-3 Dose Reductions for Lenalidomide**

| Nominal Lenalidomide Dose | Dose -1 | Dose -2 | Dose -3 | Dose -4 | Dose -5       |
|----------------------------------|----------------|----------------|----------------|----------------|----------------------|
| 25 mg Days 1-21                  | 20 mg          | 15 mg          | 10 mg          | 5 mg           | 5 mg every other day |

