#### **6.7.4 Renal Function**

Carfilzomib has not been fully characterized in subjects with creatinine clearance  $< 30 \text{ mL/min}$ . It is critical that the subject's renal function is known at the time of dosing. Renal function, serum creatinine, and serum uric acid should be monitored closely during treatment with carfilzomib. Renal function must be monitored closely during treatment with carfilzomib. Serum chemistry values, including creatinine, must be obtained and reviewed prior to each dose of carfilzomib during Cycles 1 and 2. Refer to [Table 6-8](#) for guidance regarding dose reduction in subjects with compromised renal function.

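### The renal rows of Table 6-8 disagree on when and at what dose carfilzomib and lenalidomide resume, and their fixed lenalidomide doses are not tied to the dose levels in Table 6-3

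*Protocol*

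**What the plan says.** Sections 6.3.1 and 6.7.4 of the protocol send the investigator to Table 6-8 for renal dosing. Its renal block has separate rows for CrCl above 50, 30 to 50, below 30, and below 30 on dialysis.

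- **Carfilzomib.** Above 50 and at 30-50 the entry is *Full dose*. Below 30 it is "Hold carfilzomib until CrCl > 30 mL/min; restart at 1 dose decrement". Below 30 on dialysis it is "Hold until resolved to ≤ Grade 2. Then restart carfilzomib at 1 dose decrement".
- **Lenalidomide.** Above 50 the entry is *Full dose*. At 30-50 it is "Reduce lenalidomide to 10 mg every 24 h; may reinstate prior dose if, after 2 cycles, CrCl normalizes". Below 30 it is "Reduce lenalidomide to 15 mg every 48 h". On dialysis it is 5 mg once daily, given after dialysis on dialysis days.

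Three other places bear on these rows. Table 6-2 steps carfilzomib down from 36 to 27, 20, 15 and 11 mg/m2. Table 6-3 steps lenalidomide down from 25 mg to 20, 15, 10 and 5 mg daily, then to "5 mg every other day" (Dose -5). Section 6.5 gives the general restart rule: recovery to baseline or to Grade 1 or less within 21 days, otherwise permanent discontinuation, with deviations needing the Lead Principal Investigator's approval.

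**The concern.** A dosing table should give one answer for one patient state. Here the states overlap, or follow one another as renal function changes, and the answers differ. The table does not say which row governs when two apply, what *Full dose* means for a patient who has already been reduced, or what CrCl counts as normal. Nor does it link its fixed lenalidomide doses to the dose ladder in Table 6-3.

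Consistency of treatment across sites and patient safety are at stake. Patients with CrCl below 50 are not a remote case. Inclusion criterion 11 admits by CrCl or, alternatively, by serum creatinine, so a patient below 50 can enter. Section 6.7.3 names CrCl below 50 as a marker of particularly high risk for tumor lysis.

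**Working it through.** There is no sample-size or power figure to reproduce. The check sets the rows side by side and converts each regimen to an amount.

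**1. Carfilzomib on dialysis.** The dialysis row describes a subset of the row for CrCl below 30, and no text says that it replaces that row. The release conditions are:

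- below 30: CrCl above 30 mL/min;
- below 30 on dialysis: Grade 2 or less;
- general rule, Section 6.5: baseline or Grade 1 or less.

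The renal rows are entered on a CrCl or creatinine value and name no adverse-event term, so Grade 2 has no stated referent. The wording of the carfilzomib cell is the same as in the neuropathy row of the same table. This mismatch remains whatever *Full dose* means.

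**2. Carfilzomib on recovery from below 30.** Take a patient on 36 mg/m2 who is held and then recovers to, say, 40 mL/min.

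- Row below 30: restart one level down, 27 mg/m2 by Table 6-2.
- Row 30-50, which now describes the patient: *Full dose*, 36 mg/m2 if that means nominal.
- Ratio: 36/27 = 1.33.

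**3. Lenalidomide on recovery from 30-50.** Dosing runs over Days 1-21, so a daily regimen has 21 doses.

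- Row 30-50: 10 mg daily, 10 × 21 = 210 mg per cycle, until two cycles (2 × 28 = 56 days) have passed and CrCl *normalizes*, for which no cut-off is given.
- Row above 50: *Full dose*, no wait. If that means nominal, 25 × 21 = 525 mg per cycle.
- Ratio: 525/210 = 2.5, for up to two cycles, or longer if normal is taken to mean more than just above 50.

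If *Full dose* means the patient's own prior dose, the gap is smaller. For a patient previously on 15 mg it is 15 × 21 = 315 mg against 210 mg. The two rows below 30 have no lenalidomide return rule at all.

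**4. Fixed renal doses against Table 6-3.** Dosing every other day from Day 1 gives 11 doses (Days 1, 3, ..., 21).

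| Regimen | Arithmetic | mg per 21 days |
|---|---|---|
| 10 mg daily (CrCl 30-50) | 10 × 21 | 210 |
| 15 mg every 48 h (CrCl below 30) | 15 × 11 | 165 |
| 5 mg daily (dialysis; also Dose -4) | 5 × 21 | 105 |
| 5 mg every other day (Dose -5) | 5 × 11 | 55 |

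The first two renal cells use the verb *Reduce*. For a patient already on Dose -4 or Dose -5 nothing is left to reduce to, so the dose is undefined. The dialysis cell has no such verb. Read literally, it moves a Dose -5 patient from 55 to 105 mg per 21 days (105/55 = 1.9). No sentence in the protocol says how a fixed renal dose applies to a patient already at or below it.

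**The case against.** The strongest reply is that ordinary reading resolves most of this. The more specific row governs, so a dialysis patient follows the dialysis row and a patient reduced under the 30-50 row follows that row's own return clause. *Full dose* then means only that no renal reduction applies. The table seems to use it that way elsewhere: the carfilzomib entry for a lenalidomide-related toxicity is also *Full dose*. Section 6.3.2 sets lenalidomide at 25 mg or the best tolerated dose, so full need not mean nominal. Under this reading points 2 and 3 largely disappear. It is reasonable, but the table does not state it, and several rows say *current dose* where the dose in force is meant. It also leaves the dialysis row's undefined grade, the missing cut-off for *normalizes*, and point 4.

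Four stronger readings are tempting, and the documents do not support them.

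- **Worsening renal function raises lenalidomide 1.6- to 3.8-fold.** Those ratios come from 165/105 = 1.6, 210/105 = 2.0, 165/55 = 3.0 and 210/55 = 3.8. Both cells are instructions to reduce and cannot order a rise. They leave a gap. Only the dialysis cell literally exceeds a Table 6-3 level.
- **A patient still on dialysis may restart carfilzomib.** That would require such a patient to be at Grade 2 or less. The CTCAE renal grades are not reproduced in the protocol. Its fallback severity scale in Section 8 describes Grade 2 as needing little or no medical intervention, which does not fit dialysis.
- **The background contradicts the safety text.** Section 1.5.2.1 cites a phase 1 abstract concluding that "carfilzomib can be safely administered to patients with substantial renal impairment", and Section 6.7.4 says "Carfilzomib has not been fully characterized in subjects with creatinine clearance" below 30 mL/min. A favorable early study and incomplete characterization are compatible.
- **The primary endpoint is affected.** Nothing in the documents shows this.

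Sections 6.4, 6.5 and 6.6 also limit long holds, because delays beyond 21 days lead to discontinuation unless an exception is agreed. That bounds the duration of a conflict but does not settle which row applies.

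**Conclusion.** The renal rows are internally inconsistent and should be corrected. The firmest element is the pair of carfilzomib release conditions for a dialysis patient, which rests on no assumption about *Full dose*. The recovery conflicts are conditional: 27 against 36 mg/m2 of carfilzomib, and up to 525 against 210 mg per cycle of lenalidomide, both assuming that *Full dose* means nominal and that no unstated precedence rule applies. The ladder mismatch is a gap in two rows and a literal excess in one, 105 against 55 mg per 21 days for a Dose -5 patient on dialysis. How many patients would meet these situations cannot be computed from the documents, and the Cycle 8 test is not called into question. The point concerns consistent and safe dosing.

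**What to change.** Reconcile the renal rows of Table 6-8 with each other, with Tables 6-2 and 6-3, and with the restart rule in Section 6.5. The revised text should state:

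- which row governs when a patient meets two, including a patient whose CrCl has moved from one row to another;
- one carfilzomib release condition for the overlapping rows, on a named scale, and how it relates to Section 6.5;
- what *Full dose* means for a patient already reduced, and what CrCl counts as *normalizes*;
- how each fixed lenalidomide dose applies to a patient already at or below it, and whether and how lenalidomide returns from the two rows below 30.

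While the cells are open, CrCl values of exactly 30 and exactly 50 mL/min should be assigned, since neither falls in any row now. The clinical team decides the content of each rule; this review takes no position on which dose or criterion is right. The cost is an amendment to a few cells of one table and perhaps a footnote, with no added tests, visits or patients.

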**Table 6-8 Dose Modifications for Non-hematologic Toxicity**

| Recommended Action                                                                                                                                                                                                                                        |                                                                                                                                                                                                                                                                                                                                   |                                                                                                                                                                                                                                                                                                                                 |
|------------------------------------------------------------------------------------------------------------------------------------------------------------------------------------------------------------------------------------------------------------------|-----------------------------------------------------------------------------------------------------------------------------------------------------------------------------------------------------------------------------------------------------------------------------------------------------------------------------------|---------------------------------------------------------------------------------------------------------------------------------------------------------------------------------------------------------------------------------------------------------------------------------------------------------------------------------|
|                                                                                                                                                                                                                                                                  | Lenalidomide                                                                                                                                                                                                                                                                                                               | Carfilzomib                                                                                                                                                                                                                                                                                                              |
| Venous thrombosis/embolism

≥ Grade 3                                                                                                                                                                                                        | Hold lenalidomide dose and adjust anticoagulation regimen; re-start at treating investigator's discretion at full dose                                                                                                                                                                                                            | Hold carfilzomib dose and adjust anticoagulation regimen until resolution; re-start at 1 dose level reduction recommended                                                                                                                                                                                                       |
| Hyperthyroidism or hypothyroidism                                                                                                                                                                                                                         | Omit lenalidomide for remainder of cycle, evaluate, and initiate appropriate therapy.

Restart lenalidomide next cycle at 1 dose decrement                                                                                                                                                                                  | No adjustment required                                                                                                                                                                                                                                                                                                          |
| Congestive heart failure (CHF)                                                                                                                                                                                                                                   | Any subject with symptoms of CHF, whether or not lenalidomide related, must have the dose held until resolution or return to baseline. If CHF was felt to be lenalidomide related, reinstate by one dose decrement after return to baseline. If no resolution of CHF after 2 weeks, the subject will be withdrawn from the study. | Any subject with symptoms of CHF, whether or not carfilzomib related, must have the dose held until resolution or return to baseline. If CHF was felt to be carfilzomib related, reinstate by one dose decrement after return to baseline. If no resolution of CHF after 2 weeks, the subject will be withdrawn from the study. |
| Hypertension including Hypertensive Crises                                                                                                                                                                                                                | NA                                                                                                                                                                                                                                                                                                                                | ≥ Grade 3: carfilzomib attribution, hold drug until resolved to ≤ Grade 2. Resume at one level dose reduction                                                                                                                                                                                                                   |
| Heart problems including rapid, strong or irregular heartbeat

Heart attack, reduced blood flow to the heart, abnormal amount of fluid between the heart and lining around the heart, and swelling/irritation of the lining around the heart | NA                                                                                                                                                                                                                                                                                                                                | ≥ Grade 3: carfilzomib attribution, hold drug until resolved to ≤ Grade 1. Resume at one level dose reduction                                                                                                                                                                                                                   |

